#### Administrative databases

Administrative databases will be used to evaluate whether the pathway improves health care coordination and decreases subsequent ED utilization and wait times. We will use NACRS data from each hospital to assess ED length of stay, hospital admissions, and number and frequency of repeat ED visits at 10 days and 3 months post the index ED visit. Data will be prospectively collected into a shared ED-CMHA database tool to assess CMHA service times (intake, full assessment and treatment) post-ED visit.

#### Health consumer surveys

Patient/caregiver surveys will be used to assess satisfaction with the ED visit and service within CMHAs. Because the EDMHCP recommends CMHA referral intake within 7 days, we will use structured interviews and validated measures to conduct a 10-day post-ED visit survey to assess ED visit satisfaction and whether CMHA intake has occurred. Patients or their caregivers will be contacted by e-mail, post, or phone within 7–10 days of the ED visit and will be given three follow-up measures by phone: (1) structured interview to determine if patients had initiated and received recommended MH services 10 days after being discharged from the ED; (2) the eight-item Client Satisfaction Questionnaire (CSQ-8) to determine patients’ satisfaction with heath care services received in the ED as reported by caregivers or youth; and (3) The Services for Children and Adolescent-Parent Interview (SCA-PI) which describes pediatric MH services received across multiple settings, as reported by caregivers. To reduce respondent burden, for the purpose of this study, only eight questions concerning services received for MH issues have been selected. The SCA-PI will be used to measure patients’ use of community resources and document perceptions of the ED’s role in connecting them to MH services.

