### Outcome measures

Table 4 provides a summary of study outcomes with the corresponding evaluation measures. The primary *process* outcome is the proportion of patients with documented MH-specific recommendations, as defined by the project team and based on the EDMHCP, in the medical chart. The primary MH *service* outcome is the proportion of patients that receive the EDMHCP recommended follow-up: either within 24 h or 7 days post-ED visit, based on pathway defined risk level. Recognizing logistic and scheduling factors, a successful outcome will permit a 12-h or 3-day window for follow-up. Adherence, within-window adherence, and non-adherence will be analyzed separately. Secondary outcomes include (1) EDMHCP uptake in the ED, measured as the proportion of completed clinical pathway forms filed in the health record; (2) post-ED uptake of recommended community MH services, as measured by the Services for Children and Adolescent-Parent Interview (SCA-PI) tool [21]; (3) alignment of recommended services to the HEADS-ED assessment; (4) ED length of stay, hospital admissions, ED revisits (10 days and 3 months) obtained from health records and National Ambulatory Care Reporting System (NACRS) data; and (5) patient/caregiver satisfaction with the ED visit as measured by the Services for Children and Adolescent-Parent Interview (SCA-PI) [22] and the Client Satisfaction Questionnaire (CSQ-8) [23].

**Table 4 Tab4:** Study outcomes: process and service

Outcome measure		Description	Details	Data source
Process outcomes	1°	Documented MH recommendations	Proportion of patients with documented MH-specific recommendations in the medical chart	Health record audits
	2°	EDMHCP uptake in the ED	Measured as the proportion of completed CPs filed in health records	Health record audits
Service outcomes	1°	Patients receiving post-ED follow-up	Proportion of patients that receive post-ED follow-up as per EDMHCP recommendations	Health record audits
				NACRS
				Telephone follow-up
	2°	Patient perspectives of post-ED MH service uptake	Post-ED uptake of recommended community MH services	Services for Children and Adolescent-Parent Interview (SCA-PI)
		Alignment of risk assessment with MH services recommendations	Alignment of recommended services to the HEADS-ED assessment	Health record audits
				NACRS
		Hospital metrics	ED LOS, hospital admissions, ED revisits (10 days, 3 months)	Health record audits
				NACRS

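### In the 7-day risk stratum, a phone interview on days 7–9 can miss follow-up that still counts through day 10 for the primary service outcome

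*Protocol article*

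**What the plan says.** Under Outcome measures, the primary service outcome is receipt of the recommended follow-up, "either within 24 h or 7 days post-ED visit, based on pathway defined risk level". The section then relaxes both limits: "a successful outcome will permit a 12-h or 3-day window for follow-up". It continues: "Adherence, within-window adherence, and non-adherence will be analyzed separately". Table 4 gives three data sources for this outcome: health record audits, NACRS and "Telephone follow-up".

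Under Health consumer surveys, the plan is to "conduct a 10-day post-ED visit survey to assess ED visit satisfaction and whether CMHA intake has occurred". Patients or caregivers are to be "contacted by e-mail, post, or phone within 7–10 days of the ED visit" and then given three measures by phone. The first is a "structured interview to determine if patients had initiated and received recommended MH services 10 days after being discharged from the ED". No second call is described.

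Under Administrative databases, a further source is mentioned: "Data will be prospectively collected into a shared ED-CMHA database tool to assess CMHA service times (intake, full assessment and treatment) post-ED visit". Table 4 does not list it for the primary service outcome. The same section describes NACRS as the source for length of stay, admissions and repeat ED visits.

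**The concern.** The contact window opens on day 7, but in the 7-day stratum the success window stays open until day 10. A family interviewed on day 7, 8 or 9 who says that no follow-up has taken place may still be seen in time. Their true class would then be within-window adherence, while the interview shows nothing. The exposed days, 8 to 10, are exactly the days that define that class.

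The mismatch is also internal to the survey description. One sentence allows contact from day 7 and asks a question whose reference point is day 10. An interview on days 7–9 cannot answer that question.

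At stake is the split between within-window adherence and non-adherence for a primary outcome. Any loss lowers the measured follow-up proportion, by an amount that depends on how quickly staff reach families. If that speed differed between sites or between the pre- and post-implementation periods, part of the difference would enter the effect estimate.

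**Working it through.** **The plan's own precision figure.** Health record audits gives ±2.0% for about 2503 pooled visits per period at a true proportion of 50%. Check: 1.96 × √(0.25/2503) = 1.96%, which agrees. It is used below only as a rough yardstick, because it counts expected visits and not completed telephone interviews.

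**Windows, from Outcome measures and Health consumer surveys**

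| Stratum | Target | Allowance | Success closes | Earliest contact | Days still open at earliest contact |
|---|---|---|---|---|---|
| 24-h | 24 h | 12 h | 36 h | day 7 | none |
| 7-day | 7 days | 3 days | day 10 | day 7 | up to 3 |

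Only the 7-day stratum is exposed. Within it, strict adherence (by day 7) is complete, or nearly so, at the earliest call. The exposed class is follow-up on days 8–10.

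**Chance that one interview misses a day 8–10 follow-up.** Assumptions: the interview takes place at contact, contact is equally likely on days 7, 8, 9 and 10, and follow-up is spread evenly over days 8–10. A follow-up on day v is missed if the interview falls before v.

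- v = 8: missed by a day-7 interview, 1/4 = 25%
- v = 9: missed on days 7 and 8, 2/4 = 50%
- v = 10: missed on days 7, 8 and 9, 3/4 = 75%
- Mean m = (25 + 50 + 75)/3 = 50%

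If same-day follow-up also counts as missed, the three values are 50%, 75% and 100%, with mean 75%. If every interview is on day 7, m = 100%. If every interview is at the end of day 10, m = 0.

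**Downward bias in the success proportion.** Let q be the share of patients first seen on days 8–10, and r the share of missed cases recovered from other sources. Then bias = q × m × (1 − r). The article gives none of the three. With m = 50%:

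| q (assumed) | r = 0 (telephone only) | r = 50% | r = 90% |
|---|---|---|---|
| 5% | 2.5 points | 1.25 | 0.25 |
| 10% | 5 | 2.5 | 0.5 |
| 20% | 10 | 5 | 1 |

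With telephone only, letting m run from 0 to 100% gives a bias anywhere from 0 to q.

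**Effect on a pre–post difference.** If m and r are the same in both periods, the change in the day 8–10 class is multiplied by 1 − m(1 − r). At m = 50% and r = 0 it is halved. If timing differs, a difference can appear where none exists. With q = 10% in both periods, r = 0, m = 50% in one period and 0 in the other, the spurious difference is 10% × 50% = 5 points. Nothing in the article says that timing will differ, so this last figure only shows the mechanism.

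**The case against.** A reader might infer that patients called early and seen on days 8–10 will be recorded as not followed up. The article does not support that, for four reasons.

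- No passage says that a negative answer on days 7–9 is final, is scored as non-adherence, or overrides another source.
- Telephone is one of three listed sources. The audits are to abstract enough data to judge adherence with the pathway, and the shared ED–agency database would hold intake times whenever the family is called.
- Contact may be by e-mail or post while the measures are given by phone. Contact on days 7–10 could therefore be outreach that leads to an interview on day 10, which would suit the survey's 10-day label.
- This is a condensed article. Rules for call attempts, for ranking sources and for scoring early negatives may sit in the full protocol, so their absence is not a fault.

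These points remove the certainty, and they make the telephone-only figures a worst case under the even-timing assumption. They do not remove the mismatch, which lies between stated texts. NACRS is described for hospital utilisation, and nothing says the audits capture community agency intake. Among the Table 4 sources for this outcome, only the survey is described as establishing whether that intake occurred. The shared database is not in Table 4 for this outcome, and it is not said to cover the pre-implementation period. If the outreach reading is the intended one, the text still has to fix the interview day. Even day 10 itself is safe only once that day has ended.

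**Conclusion.** The point holds in a limited form. In the 7-day stratum, the stated contact schedule opens up to three days before the outcome window closes. An interview on days 7–9 can therefore miss follow-up that still qualifies, and it cannot settle day-10 status. Exposure is confined to the boundary between within-window adherence and non-adherence in that stratum.

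The mismatch is certain from the text; the size of the bias is not. The 2.5–10 points rest on four assumptions: interview at contact, even timing over days 7–10, 5–20% of patients seen on days 8–10, and no recovery from other sources. At 90% recovery the same range becomes 0.25–1 point, below the ±2.0% yardstick. A bias in the effect estimate would follow from different call timing by site or period, which the article neither states nor rules out. Since this is a primary outcome and the remedy is cheap, it should be corrected before data collection.

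**What to change.** - Hold the outcome interview after day 10 has ended, for example on days 11–14, and align the survey's label and the interview question with that timing.
- Ask for the date and time of the first follow-up contact, and classify each patient from that record against 24 h, 36 h, 7 days and 10 days, by risk stratum.
- Do not code non-adherence from a call made before the patient's window has closed.
- Where dated agency intake records from the shared database are available for both periods, add them to Table 4 as a source for this outcome.

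The cost is a change of wording and call schedule. The article's Trial status section places the project in the pre-implementation phase, so the change can still be made. The downside is recall about four days longer for the ED satisfaction items (days 11–14 in place of 7–10). An undated negative answer from an early call, by contrast, could not be corrected afterwards from the interview itself.

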### Process evaluation

To explore reasons for potential variation across in implementation effectiveness across the study sites, we will conduct a concurrent process evaluation by documenting characteristics of our intervention, as well as the participants’ response to the delivery. This evaluation will assess the degree of variability and fidelity in implementation across the sites, revealing the degree to which the intervention addressed the relevant factors for change. Specific components of this process evaluation will include process logs, data from the post-implementation site visits, and qualitative interviews. Reasons for lack of completed implementation, should this occur at any site, will be detailed and further explored in the post-implementation phase interviews. Lessons learned will be documented and shared with site partners to promote sustained pathway use.

#### Process log

A process log will be used to longitudinally track key outcomes and capture issues related to site customization of documents, barriers and delays, workshop attendance and interest, ease of use, and degree of pathway uptake. Log components will include interim survey feedback, monthly updates from site champions, and implementation progress with negotiated target dates. Additional site support will be provided as needed, based on interim findings.

#### Site visits

Two months following completed implementation, structured site visits will be conducted to assess accessibility and operational knowledge regarding the pathway. Findings will be compared to pre-implementation visits for each site.

#### Qualitative interviews

To explore organizational issues, team dynamics and other relevant issues impacting EDMHCP implementation, post-implementation interviews will be held using TDF-based interview guides. On-site focus groups will be held with up to ten participants per organization. The focus group moderator will record field note observations. As well, KI interviews will be conducted with an administrative lead for each organization. Additional focus group sessions or KI interviews will be held if data saturation is not achieved. All interview sessions will be audiotaped and transcribed for analysis.

### Analysis

#### Quantitative analysis

Descriptive statistics (means and standard deviations for continuous variables or medians with interquartile ranges) will summarize EDs, CMHAs, and patient characteristics. Frequencies and proportions for categorical variables will be reported. We will use a multiple baseline study design and conduct interrupted time-series analysis using segmented regression models, adjusting for site, with ARIMA autocorrelation structure [25–27] to evaluate whether the EDMHCP has resulted in improved health care utilization, medical management, and health sector coordination. Two-sided *p* values less than 0.05 will be considered statistically significant. Model estimates will be tabulated, together with 95 % confidence intervals. We will also calculate hospital level summary measures including proportions in the pre- and post-intervention periods at each site and referred to each CMHA. An unweighted mean of the change from pre- to post-intervention will be calculated for each hospital ED. The main effect measure will be calculated as the difference between the mean changes in intervention.

*Qualitative analysis* is integral to determine relevant factors and experience with EDMHCP use. Pre/post-site visits, focus groups, and KI interviews will yield complex data that will inform the intervention and prepare for the EDMHCP implementation (pre) and verify EDMHCP uptake status and assess stakeholders’ experiences regarding the intervention success. Interviews will be audiotaped and transcribed. Using the TDF, two coders will independently analyze all transcripts and field notes. The analyses will be provided in an overall thematic format prior to the intervention and 6-month post-intervention. To monitor progress and pursue emerging themes, data collection and analysis will proceed iteratively and concurrently [28]. The qualitative analyst will feed relevant emerging themes back to the interviewer who will revise the interview guide as needed to capture new ideas. Inductive analysis will be managed using N-Vivo10 software and will occur in three phases: coding, using the TDF [18], and categorizing/developing themes. For consistent application, codes will be operationally defined and placed into broad categories that correspond to the major units of analysis. As categories emerge, their theoretical properties will be defined. Comparisons between multiple categories will be conducted to locate similarities and differences between them. Categories will then be synthesized into themes.

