### Project phases

The project phases and designated timelines are outlined in Table 2. Once REB approval is secured at each site, the *pre-implementation phase* will proceed with the site readiness visits and qualitative interviews that will determine the final tailored intervention strategies. The *implementation phase* for each dyad begins with a process to secure a written memorandum agreement between the ED and CMHA to ensure clarity of responsibilities and expectations integral to the pathway. Implementation will proceed as per the tailored intervention strategy. Completed pathway implementation requires, at a minimum, the following: EDMHCP site customization and committee approvals, delivery of at least two educational workshops for each organization, and EDMHCP availability in the ED. We have designated an 8-month period for EDMHCP implementation within each dyad. Following initiation within the first dyad, subsequent dyads will begin implementation in a staggered pattern every 3 months to allow for optimal study team support and incorporating learning from experience with previous dyads. In the *post-implementation phase*, qualitative interviews will explore experience with the implementation and site audits will be done to assess implementation status. We have defined the data collection periods as follows: (i) post-implementation, as the consecutive 9-month span that follows implementation completion plus an initial 3-month “settling in” time and (ii) pre-implementation, as a similar 9-month span prior to the intervention.

**Table 2 Tab2:** Description of project phases

Project phase	Duration	Activities
Pre-implementation	6 months	Site recruitment and REB approvals
		Project launch team meeting
		Site readiness visits
		Qualitative interviews and analysis
		Intervention development
		Site champion training
Implementation	17 months (8 months per dyad)	Site customization
		Forms approvals
		Clinical pathway training
		Adoption and feedback
Post-implementation	12 months	Post-implementation site visits
		Qualitative interviews and analysis
Data collection and analysis	4 months	Chart audits
		Chart to administrative database linkage
		Quantitative data analysis
Follow-up	2 months	Project partner meeting: review of findings
		Wrap-up and dissemination

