#### Health record audits

To evaluate whether the intervention results in EDMHCP use among ED clinicians and documentation of MH-specific discharge recommendations, we will audit health records of relevant patients seen during alternate weeks in each 9-month pre- and post-implementation period. ICD10 codes (F codes, mental, and behavior disorders; X codes, intentional self-poisoning and self-harm; Y codes, poisoning and self-harm of undetermined intent) listed as primary or secondary diagnoses will identify relevant patient charts during the study period. Abstracted data will include demographic and sufficient clinical data to determine risk assessment, disposition plans, and adherence with EDMHCP recommendations. Two auditors, blinded to the study aims and protocol, will be trained to abstract and directly enter health records data into REDCap, an online database [24]. A data dictionary will be created to guide auditors and ensure standardized data collection procedures. Auditors will each abstract the same 50 charts to assess inter-rater agreement. This will be measured for key variables with a kappa coefficient and further training will be done until a prevalence and bias-adjusted kappa >0.6 is achieved.

Based on historical administrative data, the number of pediatric MH visits at the pediatric specialized center is expected to be approximately 2250 during each 9-month period. This sample size will permit estimation of a proportion at this site to within ± 2.1 %, conservatively assuming a true proportion of 50 %. At the other extreme, the lowest number of pediatric MH visits during each 9-month period among the other three sites is expected to be approximately 61 at the rural hospital, which will permit estimation of a proportion to within ±12.5 %. Pooling across sites, the total sample size in each 9-month period is anticipated to be approximately 2503, which will permit estimation of a proportion to within ± 2.0 %.

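### The quoted precision counts all visits although charts are audited in alternate weeks, and it does not describe the segmented-regression effect, whose level change carries about ±18 points across an 11-month gap

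*Protocol article*

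**What the plan says.** - **Model.** Protocol article, Quantitative analysis: the interrupted time series uses "segmented regression models, adjusting for site, with ARIMA autocorrelation structure". Two-sided p "values less than 0.05 will be considered statistically significant". The same paragraph plans pre and post proportions per hospital and an unweighted mean change for each ED, and then defines a main effect measure in terms of mean changes.
- **Windows.** Project phases: post-implementation data are "the consecutive 9-month span that follows implementation completion plus an initial 3-month" settling-in time; the comparison block is "pre-implementation, as a similar 9-month span prior to the intervention". Between them, "We have designated an 8-month period for EDMHCP implementation within each dyad". Dyads are offset: "subsequent dyads will begin implementation in a staggered pattern every 3 months".
- **Sampling.** Health record audits: the plan is to "audit health records of relevant patients seen during alternate weeks in each 9-month pre- and post-implementation period".
- **Counts and precision.** The same section expects about 2250 visits per 9 months at the paediatric centre (±2.1%) and about 2503 pooled (±2.0%). For the rural hospital, "the lowest number of pediatric MH visits during each 9-month period among the other three sites is expected to be approximately 61" (±12.5%).

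The article gives no precision or power figure for a level or slope change.

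**The concern.** The only precision the reader is given answers a question the analysis does not ask. It concerns one proportion in one period, and it counts charts that will not be read. The analysis estimates a change, and the segmented model estimates it by extending a slope fitted on 9 months over 11 months without audited charts. That extrapolation dominates the uncertainty.

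The risk lies in interpretation. A non-significant level change could be read as a failure of the pathway when the contrast could not have excluded a change of well over ten points. The primary process outcome is fully exposed, because its only listed source is the health record audit.

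**Working it through.** **Inputs from the article.** Visits per 9 months: 2250, 61 and 2503 pooled. By subtraction, the two remaining sites share 2503 − 2250 − 61 = 192. Each has at least 61, because 61 is the lowest, and so at most 131. True proportion 50%. Audit in alternate weeks, taken as half of visits. Gap 8 + 3 = 11 months, which is a minimum if the pre block ends before implementation starts.

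**1. The stated figures reproduce on all visits.** Half-width = 1.96 × √(0.25/n).

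| Site | All visits: n, half-width | Audited (n/2): n, half-width |
|---|---|---|
| Paediatric centre | 2250, ±2.07% | 1125, ±2.9% |
| Rural hospital | 61, ±12.55% | 30.5, ±17.7% |
| Pooled | 2503, ±1.96% | 1251.5, ±2.8% |

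**2. Simple pooled pre-post change.** 1.96 × √(2 × 0.25/1251.5) = ±3.9 points on audited charts (±2.8 if every visit were audited).

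**3. Segmented level change, pooled audited charts.** Assumptions: monthly points, a level and a slope change, no autocorrelation. Charts per month: 1251.5/9 = 139, so σ = √(0.25/139) = 4.24 points. Pre months are 1–9 (mean 5) and post months 21–29 (mean 25). The squared deviations within each block sum to 60.

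- Start of the post block: SE = 4.24 × √[1/9 + (21−5)²/60 + 1/9 + (21−25)²/60] = 4.24 × √4.756 = 9.25, so **±18.1 points**.
- Middle of the post block: 4.24 × √[1/9 + (25−5)²/60 + 1/9] = 11.13, so ±21.8 points.
- Adjacent blocks (post starting in month 10): 4.24 × √[1/9 + 5²/60 + 1/9 + 4²/60] = 4.04, so ±7.9 points. The gap alone widens the interval 18.1/7.9 = 2.3 times.

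**4. Sensitivity.**

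- Weighted regression with site intercepts, half-month points and the staggered windows (two unnamed sites assumed at 96 visits each, paediatric centre first): ±17.7.
- The same with an assumed autocorrelation of 0.3: ±22.5.
- The same with one annual harmonic and no autocorrelation: ±22.7.
- One common slope and no slope change (monthly points, as in step 3): ±15.7.
- If the quoted counts were already audited charts: 18.1/√2 = ±12.8.

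**5. Sparsity by site.** Nine months is 39.1 weeks. Charts per audited week are 61/39.1 = 1.6 at the rural hospital, at most 131/39.1 = 3.4 at the other two small sites, and 2250/39.1 = 57 at the paediatric centre, which supplies 2250/2503 = 90% of visits. The site-level level change scales from step 3: rural 18.1 × √(1251.5/30.5) = ±116 points; a site with 131 visits, 18.1 × √(1251.5/65.5) = ±79 points. Neither is informative.

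**6. Unweighted mean over four sites.** With the two unnamed sites at 96 visits each: 1.96 × √[0.5 × (1/1125 + 1/30.5 + 1/48 + 1/48)]/4 = ±9.5 points on audited charts. The weighting of the main effect therefore matters.

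**The case against.** The strongest reply is that the article's precision statement is correct for what it claims, a single proportion, and is never assigned to the time-series effect. That stands. A reader might infer that ±2.0% was promised for the level change, but the text does not say so. What remains is that the figures count unaudited charts and that no figure covers the contrast of interest.

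Second, the article states neither a time unit nor a weighting. A reader might infer that rural weeks with one or two charts will count as much as weeks with 57, or that skipped weeks rule out ARIMA errors. Neither is supported. Monthly or pooled series largely avoid empty points, weights can be applied, and likelihood fitting can accommodate missing points. Such detail may sit in the full plan. The 11-month gap remains whatever unit is chosen.

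Third, season. A reader might infer that 9-month blocks cannot support a seasonal term. They can. With contiguous windows the two blocks at one site together cover all twelve calendar months, and the stagger adds information; the cost is precision (step 4). Moving the pre block to the same calendar months, 24 months before the post block, looks attractive but backfires if time and season terms stay in the model. On 139 charts per month at a single set of windows, the period effect with a linear trend and an annual harmonic goes from ±21 to ±63 points.

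Fourth, the main effect measure is already worded as a change in means, so ±18 points is not its precision. That also stands, and it shapes the fix.

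Finally, the alternate-week limit applies to chart audits. Length of stay, admissions and revisits from NACRS are not subject to it.

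**Conclusion.** The point holds in a limited form. Precision is overstated for audited charts (about ±2.9%, ±17.7% and ±2.8% instead of ±2.1%, ±12.5% and ±2.0%), and no stated figure describes an effect. The pooled segmented level change has a half-width of about ±18 points. The range is about ±13 if the counts are already audited charts to about ±23 with modest autocorrelation or an annual term. A simple pooled pre-post change has about ±3.9. Segmented results from the three small sites alone are uninformative.

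This rests on a 50% proportion, half of visits audited, a pre block ending when implementation starts, and a model with level and slope changes. The documents do not support saying that the model cannot be fitted, that season cannot be handled, or that the article claims ±2.0% for the time-series effect.

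**What to change.** 1. In Health record audits, restate precision on audited charts, for the pre-post change and for the segmented level change separately.
2. Analyse chart-audit outcomes with patient-level binomial regression containing site, period and a common seasonal term, with week-level clustered or random-effect errors. Sparse weeks then carry the weight their charts warrant.
3. Name the pre-post change as the primary estimate, clarify the sentence that defines the main effect measure, and state whether sites are pooled or weighted equally (±3.9 against ±9.5 points).
4. Report the segmented level and slope changes, with intervals, as a supporting trend analysis, and do not interpret them for the three small sites separately.
5. Leave the pre window where it is. State that NACRS outcomes are not limited to alternate weeks.

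**Cost.** Wording and model specification only, with no extra charts. The drawback is that a pre-post change assumes no secular trend, which the supporting analysis can check only imprecisely. The stagger helps little here: counted from the first dyad's start, the last pre block ends at month 9 and the first post block opens at month 11, so no dyad serves as a concurrent pre-period comparison for another. The report should say so.
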